#### Semen analyses

A semen analysis will be performed using both manual analyses (by an andrologist) and computer-aided sperm analysis under WHO criteria. The clinical andrologist will have passed the quality assurance test (UK National External Quality Assessment Services [NEQAS]) to make sure he is up to standard. Semen parameters include volume, motility, viability, concentration, morphology, and total sperm count, and another physical status will be measured. A repeat semen analysis will be performed at 3 and 6 months after the treatment to assess the response duration.

#### Blood tests

Hormone FSH and testosterone will be tested, because the levels of the two hormones are closely related to the testis function. Complete blood picture and liver and renal functions tests will also be included to assess the safety of both the TCM formula and placebo.

#### Sperm DNA fragmentation

DNA integrity has been shown to be strongly associated with reduced fertility in males. The increment of DNA fragmentation level reduces fertility in men and affects subsequent embryo development. The level of sperm DNA fragmentation will be analyzed by DNA fragmentation assay to distinguish the effect of the TCM.

#### Sperm cryotolerance

Cryopreservation of sperm is a common clinical procedure for ART treatment; some of the patient’s samples show better sperm cryotolerance than others. Cryotolerance is a test to demonstrate if sperm can tolerate the freeze-thaw procedure; the value is useful to predict the percentage of sperm surviving from cryopreservation for subsequent ART treatment. This test also indirectly provides information on sperm robustness.

#### Endocrine-disrupting chemicals test

Estradiol-like substances in the formula or placebo can possibly reduce the therapeutic effect in males [10, 11]. We will use a patented estrogenic testing method to test the analogs of the WZYZ formula and placebo.

#### DNA maturity assay

Sperm DNA maturity will be tested using aniline blue solution staining. The solution stain histone protein is replaced by protamine during spermatogenesis for dense sperm head compaction. A high histone content indicates poor embryo development and pregnancy outcome.

#### ART outcomes

The ART outcomes include fertilization rate, embryo quality, blastocyst rate, implantation rate, and pregnancy rate. These data will be recorded in the treatment record if the patient receives ART in our hospital. If the patient receives ART elsewhere, the outcomes will be recorded by our team research nurse during a 2-year follow-up.

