### Outcome measurements

The primary outcome is to compare the TMS count, natural conception rate, pregnancy outcome, and live birth rate. Secondary objectives are sperm functions and assisted reproductive technology (ART) outcome as well as the safety assessment on the TCM formula.

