#### Retention

Once a participant is enrolled, our study investigators and staff will provide written feedback of their semen analysis and liver and kidney function tests. Our research assistant will maintain the participant’s interest in the study through weekly follow-up phone calls, remind the participant of upcoming doctor/data collection appointments, and record the presence of any adverse drug reactions.

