### Data analysis

All the data are reported as percentages for nominal data or means ± standard deviation (SD) for continuous data. Patients with less than 70% compliance (i.e., out of 90 days treatment taking the WZYZ formula, less than 63 days of treatment completed) will be excluded. They will be considered as having dropped out and will not be included in the final analysis, but will be included in the intention-totreat analysis. The compliance will be checked by our research staff based on the patient diary and phone calls every 2 weeks. For non-compliance and missing outcomes, we will use two sets of analyses. The full analysis set (FAS) will include all patients who are randomized and will be conducted according to the intention-to-treat principle. The per protocol set will include all patients of the FAS who complete follow-up and do not have serious protocol violations.

For the baseline comparison, the independent Student *t* test or the Mann-Whitney *U* test is used to evaluate the mean or median differences between the placebo and intervention groups for continuous data depending on whether the data are normally distributed, and the chi-squared test is used for frequency comparison. For longitudinal data with a baseline, we will use repeated measures analysis of covariance (ANCOVA) to evaluate the mean difference between and within groups. All the tests are two-tailed, and the significance level is defined as a value of < 0.05.

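### ART outcomes exist only for couples who receive ART after randomisation, so a between-arm difference in them may be biased in either direction

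*Protocol article*

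**What the plan says.** The Outcome measurements section gives the role of these data: "Secondary objectives are sperm functions and assisted reproductive technology (ART) outcome as well as the safety assessment on the TCM formula". The same section states what the treatment is meant to change: "The primary outcome is to compare the TMS count, natural conception rate, pregnancy outcome, and live birth rate".

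The ART outcomes section lists the measures: "The ART outcomes include fertilization rate, embryo quality, blastocyst rate, implantation rate, and pregnancy rate". It then says whose data are collected. For the trial's own unit: "These data will be recorded in the treatment record if the patient receives ART in our hospital". For other units: "If the patient receives ART elsewhere, the outcomes will be recorded by our team research nurse during a 2-year follow-up". Table 1 contains no ART step, so having ART is an unscheduled event after randomisation.

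Two other sections bear on the point. Under Retention, "our study investigators and staff will provide written feedback of their semen analysis and liver and kidney function tests", so men learn their own semen results. Under Data analysis, "The full analysis set (FAS) will include all patients who are randomized".

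**The concern.** Randomisation makes the arms comparable for outcomes that every randomised man can have. Fertilisation rate, embryo quality, blastocyst rate and implantation rate do not exist without an ART cycle, so the full analysis set cannot be applied to them as defined. The comparison falls back on the men whose couples had ART.

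The protocol itself gives two routes by which treatment could alter that group. Natural conception is one of the primary outcomes, and couples who conceive naturally have less reason to start ART. Semen results are also fed back to participants, so a changed count could influence the choice of ART. If the trial's hypothesis is right, the two groups of ART recipients differ in composition because of treatment. A secondary result on fertilisation, implantation or ART pregnancy could then agree or disagree with the primary result for reasons unrelated to sperm function.

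**Working it through.** The protocol has no figure on this point to reproduce. It gives no natural conception rate, ART uptake or ART success rate. Every rate below is an assumption; only the total of 286 comes from the document (143 per arm at 1:1).

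**Illustration 1: one shared prognosis.** Let couple prognosis u be standard normal. Natural conception and ART pregnancy are both logistic in u with the same slope b. Intercepts are set so that natural conception is 15% (placebo) or 30% (active) and the average ART pregnancy chance is 35% in both arms, so there is no treatment effect on ART success. All non-conceivers go to ART. The observed ART pregnancy rate in an arm is

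E[(1 − p_nat(u)) × p_ART(u)] / E[1 − p_nat(u)].

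| Slope b | Placebo | Active | Gap (points) |
|---|---|---|---|
| 0.5 | 34.2% | 33.4% | 0.8 |
| 1 | 32.3% | 30.0% | 2.3 |
| 1.5 | 30.3% | 26.3% | 4.0 |
| 2 | 28.6% | 23.2% | 5.4 |

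With b = 0 both arms show 35% and there is no bias.

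**Illustration 2: two prognosis groups.** Half the couples have good prognosis and half poor. Of non-conceivers, 70% go to ART, with ART pregnancy 50% (good) or 25% (poor) in both arms. The rate per ART recipient is 0.50 × s + 0.25 × (1 − s), where s is the good-prognosis share: s = (1 − c_good) / [(1 − c_good) + (1 − c_poor)], and c is natural conception.

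Placebo, c = 20% and 5%: s = 0.80 / (0.80 + 0.95) = 0.457, so the rate is 36.4%.

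| Natural conception on active (good, poor) | s | Active rate | Placebo rate |
|---|---|---|---|
| 40%, 5% | 0.60 / 1.55 = 0.387 | 34.7% | 36.4% |
| 60%, 5% | 0.40 / 1.35 = 0.296 | 32.4% | 36.4% |
| 20%, 25% | 0.80 / 1.55 = 0.516 | 37.9% | 36.4% |
| 20%, 5% (no effect) | 0.457 | 36.4% | 36.4% |

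If instead conception is 10% in both groups on placebo and 30% in both on active, s stays at 0.50 and the rate is 37.5% in both arms. Benefit in the good-prognosis group biases against active, benefit in the poor-prognosis group biases towards it, and an even effect leaves no bias.

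**Does changing the denominator cure it?** No. ART pregnancies per randomised man equal uptake among the randomised times the rate above. In the even-effect case this is 0.90 × 0.70 × 0.375 = 23.6% on placebo against 0.70 × 0.70 × 0.375 = 18.4% on active. It falls only because more couples conceived naturally.

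**Pregnancy by any route per randomised man.** In the first row of the second table (40%, 5%), placebo is 12.5% natural + 22.3% ART = 34.8%, and active is 22.5% + 18.8% = 41.3%. This outcome is defined for everyone randomised.

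**Bias against sampling error.** In illustration 1 with 143 per arm, ART recipients number 143 × 0.85 = 122 and 143 × 0.70 = 100. At slope 1 the standard error is √(0.323 × 0.677 / 122 + 0.300 × 0.700 / 100) = 6.2 points, so the 2.3-point gap is 0.38 standard errors. At slope 2 it is 5.4 / 5.9 = 0.91. The chance of a significant two-sided 5% result against active rises from 2.5% to 5.6% and 14.7%; with half of non-conceivers going to ART, to 4.5% and 9.4%.

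**The case against.** The strongest reply is that the protocol does not fix the analysis being criticised. The Data analysis section names tests for baseline comparisons and repeated measures ANCOVA for longitudinal data, but no test, denominator or efficacy claim for ART outcomes. Whether such measures are tested or described is often settled in an analysis plan, which is not shown. This stands in part: a reader might infer that the trial has committed itself to a formal test among ART recipients, and the document does not say so. But the conditioning is in the outcome definition, and the outcome is a stated secondary objective of a randomised superiority trial. An analysis plan cannot give a fertilisation rate to a couple without ART.

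A second reply concerns direction and size. A reader might infer that the bias must run against the active arm and make an effective treatment look harmful. The documents do not support that. The negative sign in illustration 1 comes from assuming one prognosis that drives both outcomes with equal slopes. The two-group example reverses the sign when poor-prognosis couples benefit and removes the bias when the effect is even. The shifts shown in illustration 1 are also smaller than one standard error at the trial's size. This objection stands, and the point is limited accordingly.

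A third reply is that natural conception is only one of several primary items and the sample size rests on TMS count. That is correct, but it remains an outcome the treatment is meant to raise.

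**Conclusion.** The point holds in a limited form. At least four of the five ART measures are undefined for couples without ART, and receipt of ART is a post-randomisation event that treatment may influence. A between-arm difference in these measures is therefore not protected by randomisation and may be biased in either direction.

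The 0.8 to 5.4 points against active is an illustration. It rests on an assumed shared prognosis, natural conception of 15% against 30%, a 35% average ART pregnancy chance, ART for all non-conceivers and no effect on ART success. There is no bias if treatment affects neither conception nor ART uptake, or if it removes the same proportion of would-be ART couples from every prognosis group. Because the outcome is secondary and the illustrated bias is mostly below sampling noise, this is a desirable improvement and not a threat to the trial's main result.

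**What to change.** In the Outcome measurements and ART outcomes sections:

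1. Reconcile the follow-up for conception. The abstract, Study process and Table 1 give a further 6 months; the Natural conceptions and pregnancy outcome section gives 2 years, and ART outcomes obtained elsewhere are also followed for 2 years. State one common window.
2. Add, as the randomised comparison, pregnancy by any route (natural or ART) per randomised man within that window. Extend it to live birth only if live birth after ART is also recorded; the ART list stops at pregnancy rate, and live birth follow-up is described under natural conception.
3. Report the number starting ART by arm.
4. Present the five ART measures descriptively, without efficacy claims.

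The cost is a few lines of wording, plus one extra follow-up item if live birth is included. The trial gives up a formal efficacy claim from ART-cycle measures, and the any-route outcome answers a different question from how well sperm perform in ART.

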#### Retention

Once a participant is enrolled, our study investigators and staff will provide written feedback of their semen analysis and liver and kidney function tests. Our research assistant will maintain the participant’s interest in the study through weekly follow-up phone calls, remind the participant of upcoming doctor/data collection appointments, and record the presence of any adverse drug reactions.

### Sample size calculation

Our andrology unit conducted 892 semen analyses in 2017, in which 273 patients were diagnosed with oligoasthenospermia, and the mean of the TMS count of all patients failed to fulfill WHO criteria (5th edition, < 20 million per ejaculate) is 8.08 ± 6.19 million TMS. To detect 100% (double the TMS) improvement by the WZYZ TCM formula and accepting a type I error of 0.05 and a type II error of 0.2, the number of subjects to be recruited into each arm to detect a significant difference is 115 on each arm (Medcalc®, Version 15.6.1). To allow for a dropout/non-compliance rate of 20%, the number of subjects required in each arm is therefore 181, and the total number of subjects required in the study is 286. Therefore, the whole recruitment takes approximately 12–18 months to finish.

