### Trial design and setting

This is a prospective, randomized, placebo-controlled, double-blinded, superiority trial with a 1:1 allocation ratio. It is conducted at Assisted Reproductive Technology Unit, Department of Obstetrics and Gynaecology, Faculty of Medicine, The Chinese University of Hong Kong. Our department conducted 892 semen analyses in 2017, in which 273 patients were diagnosed with oligoasthenospermia under the WHO criteria. The Standard Protocol Items: Recommendations for Interventional Trials (SPIRIT) checklist is provided as Additional file 4.

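### The sample size inputs for total motile sperm count give about 10 or 11 men per arm, not 115, so the stated effect, SD and n are mutually inconsistent

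*Protocol article*

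**What the plan says.** All of the inputs, and the result, stand in one paragraph of the protocol article (Methods, Sample size calculation).

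- **Mean and spread:** in the unit's patients below the 20 million threshold, the mean "is 8.08 ± 6.19 million TMS". The Data analysis section reports continuous variables as "means ± standard deviation (SD) for continuous data", so ± is read as an SD.
- **Target effect:** "To detect 100% (double the TMS) improvement by the WZYZ TCM formula".
- **Error rates:** "accepting a type I error of 0.05 and a type II error of 0.2". Data analysis adds: "All the tests are two-tailed, and the significance level is defined as a value of < 0.05".
- **Design:** a "superiority trial with a 1:1 allocation ratio" (Trial design and setting).
- **Result:** "the number of subjects to be recruited into each arm to detect a significant difference is 115 on each arm", attributed to MedCalc.

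The paragraph then allows for 20% dropout or non-compliance and arrives at 181 per arm and 286 in total. No other SD, effect size or event rate for the calculation appears anywhere in the article.

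**The concern.** Doubling a mean of 8.08 million is a difference of 8.08 million, or 1.3 SDs on the stated SD. An effect that large needs only a handful of men per arm, so 115 looks wrong at sight. This paragraph is the only place where the protocol declares the effect it is designed to detect. If its inputs do not produce its n, a reader cannot tell what the trial is sized for, and the data monitoring committee or an ethics committee cannot see why 230 evaluable men are needed. A reader would also take a doubling to be roughly the smallest effect the trial can reliably detect, whereas on the stated SD it can detect much smaller ones.

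**Working it through.** **Inputs.** Difference Δ = 16.16 − 8.08 = 8.08 million; SD σ = 6.19 million; two-sided α = 0.05 (z = 1.960); power 80% (z = 0.8416); 1:1 allocation.

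**Step 1: try to reproduce 115.** Normal approximation for two means:

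n per arm = 2 (1.960 + 0.8416)² (σ/Δ)² = 2 × 7.849 × (6.19/8.08)² = 2 × 7.849 × 0.5869 = 9.2, so 10.

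The two-sample t test, with standardised difference 8.08/6.19 = 1.305, gives 10.27, so 11 (power 0.83 at 11). The stated 115 is not reproduced; 115/11 is about 10.5 and 115/10 is 11.5.

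**Step 2: try other conventions.** The cases that depart from the stated SD are assumptions made for this check, not taken from the protocol.

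| Variant | n per arm |
|---|---|
| One-sided test | 8 |
| Power 90% / 95% | 13 / 16 |
| Change score with SD × √2 | 19 |
| SD doubled to 12.38 in the treated arm only | 23.03, so 24 |
| SD doubled to 12.38 in both arms | 36.9, so 37 (t test 38) |
| Log-normal scale, stated CV / CV doubled | 16 / 40 |
| Mann-Whitney efficiency allowance | about 12 |
| Bonferroni for 2 to 5 primary outcomes | 12 to 14 |
| Paired comparison | 5 |
| ± read as a standard error from 273 men | about 2,500 |

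None of these gives 115.

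**Step 3: run it backwards.** With 115 evaluable men per arm:

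- Detectable standardised difference at 80% power: 2.8016 × √(2/115) = 0.369.
- At SD 6.19: 0.369 × 6.19 = 2.29 million, which is 2.29/8.08 = 28%.
- At an assumed SD of 12.38 (twice the stated value): 4.57 million, or 57%.
- Power for a doubling: above 99.9% at SD 6.19, and 99.85% at SD 12.38.
- SD at which a doubling would need 115 per arm: 21.9 million by the normal approximation (8.08/0.369) and 21.8 million by the t test, about 3.5 times the stated SD.

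**Step 4: the enrolment figures that follow.** 115/(1 − 0.20) = 143.75, so 144 per arm and 288 in total. The paragraph gives 181 per arm, which implies 362, and 286 in total, which implies 143 per arm. The total is close to a correct inflation of 115; the per-arm figure is not.

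**The case against.** Four objections deserve an answer.

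**The document does not show which element is wrong.** This stands. A reader might infer that the doubling is misstated, because 115 fits a 28% improvement at SD 6.19. But the SD could be the wrong element, or n could be, or 115 could come from another endpoint. The Outcome measurements section lists natural conception, pregnancy outcome and live birth as primary outcomes beside TMS. A calculation on proportions is possible: doubling a rate of 16% to 17% needs 103 to 123 per arm, depending on the rate and on whether a continuity correction is used. The article gives no such rate, so this is only a possibility.

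**A larger SD might be realistic.** It is tempting to say that no plausible SD could give 115. The document does not support that. The 6.19 comes from men selected to be below 20 million, whereas TMS at follow-up has no such ceiling, so the follow-up SD may well be larger. No follow-up SD is given. An SD of 21.8 million is large beside means of 8 and 16 million, but these pages cannot rule it out. They show only that it is not the SD the protocol used.

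**The error is on the safe side.** This also stands for the stated target. On the stated inputs the trial is oversized for a doubling, not underpowered, and the TMS comparison is not invalidated.

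**A significant result can fall below the target in any trial.** True: at 80% power, significance is reached at about 70% of the target difference (1.960/2.8016). The fault here is the mismatch between the stated inputs and n, not that general feature.

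None of this makes the sentence correct as it stands.

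**Conclusion.** The sample size statement is wrong as written. On the protocol's own mean, SD, target, two-sided α and power, about 10 or 11 men per arm are needed, against a stated 115. What is established is a mutual inconsistency between effect, SD and n, with its source unknown. It rests on reading ± as an SD, as the Data analysis section does, and on a two-group comparison of means.

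The practical consequence is that the trial's detectable effect is not the one declared. The declared basis for the sample size should be corrected because it is the only one the article gives.

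**What to change.** 1. Recover the original MedCalc calculation and identify which input or output was transcribed wrongly. If 115 came from another endpoint, name that endpoint and give its rates.
2. Remove the statement that 115 per arm is what a doubling requires at SD 6.19, and restate n from the corrected inputs.
3. If 115 evaluable men per arm is kept, say what it detects. Possible wording: *With 115 evaluable men per arm, the trial has 80% power (two-sided α 0.05) for a difference in TMS count of 2.3 million (28% of 8.08 million) if the SD is 6.19 million. Because that SD comes from men selected below 20 million, we also considered, as an assumption, a follow-up SD twice as large (12.38 million), for which the detectable difference is 4.6 million (57%).* The sponsor should add whether differences of that size matter clinically, since the protocol does not say so now.
4. Reconcile the enrolment figures in the same edit. With 115 evaluable and 20% loss, they become 144 per arm and 288 in total.

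**Cost.** If 115 evaluable per arm is retained and the total is about 288, the change is to wording: no additional patients beyond roughly the 286 already stated, and a different justification from the one now published. If the recovered calculation shows that n itself is the error, the enrolment target would have to be revisited.

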### Trial status

This trial is at Version 1.3, 16/10/2018 (ChiTR). The actual study start date was 27/02/2018; the anticipated study end date is 31/01/2022. The recruitment start date was 27/02/2018; the anticipated recruitment end date is 31/01/2020.

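### The stated enrolment target contradicts itself: 181 per arm is 362 men, but the stated total is 286, and 115 per arm with 20% dropout gives about 144 per arm

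*Protocol article*

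**What the plan says.** All the figures are in the protocol article.

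- **Sample size calculation, inputs.** The mean total motile sperm (TMS) count and its SD are given in the phrase "is 8.08 ± 6.19 million TMS". The target effect is a doubling: "To detect 100% (double the TMS) improvement by the WZYZ TCM formula". The error rates are set by "accepting a type I error of 0.05 and a type II error of 0.2". The result is 115 men per arm.
- **Sample size calculation, dropout step.** The allowance is introduced by "To allow for a dropout/non-compliance rate of 20"%, and the conclusion is that "the number of subjects required in each arm is therefore 181, and the total number of subjects required in the study is 286". The section then infers a recruitment period of roughly 12–18 months.
- **Trial design and setting; Randomization and allocation concealment.** There are two arms, allocated 1:1, in one assisted reproduction unit.
- **Data analysis.** Testing is two-sided: "All the tests are two-tailed, and the significance level is defined as a value of < 0.05".
- **Trial status.** Recruitment opened on 27/02/2018, and "the anticipated recruitment end date is 31/01/2020".

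No other section gives a sample size that would reconcile 181 with 286.

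**The concern.** The per-arm and total figures stand in the same sentence and are incompatible under equal allocation. One sentence thus supports two enrolment targets, 286 and 362.

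The target sets when recruitment stops, and recruitment had already opened when the article was written. A reader could justify closing at 286 or continuing to 362 and cite the protocol either way. The value of fixing a sample size in advance is that this choice is not left open. The target is also the figure against which accrual and the final report will be judged.

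The error lies in running prose, so it is neither a broken table nor a redaction. It is a wrong statement, not a detail left to the analysis plan.

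**Working it through.** **Inputs from the protocol article:** 115 per arm before dropout; 20% dropout/non-compliance; 1:1 allocation; 181 per arm and 286 in total after dropout.

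**Step 1. Do the two stated figures agree?**
- 2 × 181 = 362, against a stated 286. The difference is 76 men, and 76/286 = 27%.
- 286/2 = 143 per arm, against a stated 181. The difference is 38 per arm.

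**Step 2. Which figure follows from 115 and 20%?** The usual inflation is n/(1 − d).
- 115/(1 − 0.20) = 143.75. Rounded up, this is 144 per arm and 288 in total.
- Rounded down in each arm, it is 143 per arm and 286 in total. This reproduces the stated total. The retained number is then 143 × 0.8 = 114.4 per arm.
- The common variant n × (1 + d) gives 115 × 1.2 = 138 per arm and 276 in total, which matches neither stated figure.

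**Step 3. What would 181 require?**
- Implied attrition is 1 − 115/181 = 36.5%, against the 20% stated.
- For comparison, 286 implies 1 − 230/286 = 19.6%.
- Applying the 20% allowance twice gives 115/0.8/0.8 = 179.7, or 180 per arm. That is close to 181 but not equal to it. The text mentions no second allowance, and 180 per arm would not give 286 either.

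| Per arm | Total | Attrition implied if 115 remain | Relation to the text |
|---|---|---|---|
| 181 | 362 | 36.5% | stated per arm; contradicts total |
| 143 | 286 | 19.6% | stated total; 143.75 rounded down |
| 144 | 288 | 20.1% | 143.75 rounded up |

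**Step 4. Is 115 itself reproducible?** For two means, two-sided 0.05 and 80% power:

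n per arm = 2 × (1.96 + 0.84)² × SD² / difference²

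- With SD 6.19 and difference 8.08 (100% of the mean), n = 9.2, so 10 per arm. One-sided testing gives 8.
- If the SD doubled to 12.38 in the treated arm, n = 23.03, so about 23 per arm.
- Conversely, 115 per arm detects about 6.19 × √(2/115) × 2.80 = 2.29 million, which is 28% of 8.08.

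So 115 does not follow from the stated inputs. Steps 1 to 3 take it as given.

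**Step 5. Recruitment period.** From 27/02/2018 to 31/01/2020 is about 23 months. The sample size section says 12–18.

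**The case against.** The strongest defence is that this is one wrong number. The total of 286 follows from 115 and 20% with rounding down, so a sponsor working to 286 would run the trial that the inputs describe, and 181 would never be used. Most of this stands: the total is coherent and 181 is the outlier. It does not remove the contradiction, because 181 is stated as the requirement per arm and nothing in the document tells the reader to ignore it. Nor does the document show how 181 arose. If it was intended, the trial needs 76 more men.

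Four stronger readings are tempting, and the document does not support them.

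- **The 286 against 288 gap as a second error.** It is rounding. Having 114.4 evaluable men per arm in place of 115 has no material effect on power.
- **Different sites recruiting to different targets.** The trial is run in a single unit, so this cannot happen. Nor does the document tie the amount of product made to either figure.
- **Recruitment in 12 months as impossible.** A reader might note that "273 patients were diagnosed with oligoasthenospermia under the WHO criteria" in 2017, and that 286 exceeds 273. But that diagnosis is not the entry criterion, which is fewer than 20 million total progressive motile sperm, subject to exclusions. The number of men meeting it is not given. The Recruitment section also expects four to five new analyses a day. Assuming about 250 working days, that is 1,000–1,250 a year. At the 2017 proportion (273/892 = 30.6%), this gives about 306–383 men, of whom 286 would be 75–93%. That is optimistic, but it is not shown to be impossible.
- **A required consent rate.** Any rate calculated on 273 men a year has the same unsuitable denominator, so the sponsor should not be asked to print one.

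**Conclusion.** The contradiction is real and can be seen within one sentence. Under 1:1 allocation, 181 per arm and 286 in total differ by 76 men, or 27% of the stated total. Given 115 evaluable per arm and 20% loss, the consistent pairs are 144/288 or, rounded down, 143/286 with about 114 evaluable per arm. The figure out of line is 181.

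This rests on taking 115 and 20% as stated. It is a finding about the dropout step only. A reader might infer that 288 is therefore the right sample size, but that does not follow: the stated mean, SD and effect give about 10 per arm, so 115 needs its own justification.

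The recruitment period is a minor inconsistency between two statements, 12–18 months and about 23 months. It does not show that either target is unattainable.

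The sentence should be corrected because it sets the trial's stopping number and the correction costs almost nothing.

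**What to change.** 1. Check the original sample size output and establish where 181 came from.
2. If the 20% allowance on 115 is what was meant, delete 181 and state one consistent pair: either 144 per arm and 288 in total, or 143 per arm and 286 in total with about 114 evaluable per arm.
3. State the basis for 115 separately, so that correcting the dropout step is not read as confirming the base figure.
4. Reconcile the 12–18 months with the dates under Trial status.

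**Cost.** Keeping 143/286 is a change of wording only. Adopting 144/288 adds two men to the stated total. If the check shows that 181 per arm was intended, the total becomes 362, which is 76 more men, and the 20% allowance would then need a different explanation.
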